### Assumptions

We assume the prevalence of our modified Beaugerie definition of disabling disease will be approximately 55%–60%; this is informed primarily by the external validation cohort^37^ of the Beaugerie descriptors, in which 57% of 361 participants had developed disabling disease by 5 years. In support, a local audit of 33 newly diagnosed patients at one METRIC recruitment centre found 5 of 33 (15%) patients met the definition by mean 11.3 months, giving 16% at 1 year. Extrapolation to 5 years gives 58% prevalence, similar to that expected from the literature.^37^ We assume that development of disabling disease is approximately linear over time. Therefore, 207 participants will provide 114–124 events and 83–93 non-events (defined by non progression to disabling disease); the smaller proportion defines the minimum sample size for powering a modelling study, where regression methods are used for development (see section below).

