### Sample size and justification

The sample size was based on including 207 participants newly diagnosed with CD. During the study, due to problems obtaining consent for additional follow-up hampered by COVID-19, the original target recruitment was necessarily reduced from 167 to 131 from the METRIC prospective cohort, and so an increased target of 76 participant retrospective cohort recruited from METRIC sites is anticipated. We anticipate this sample size will provide between 114 and 124 events (83–93 non-events). The number of the retrospective cohort will be increased to meet the 207 participant target if recruitment to the METRC cohort is below 131.

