### Statistical methods—outcomes

#### Primary outcome

Comparative predictive ability of prognostic models incorporating MRE severity scores (MEGS, sMaRIA and Lémann index) versus models using standard characteristics alone to predict disabling CD (modified Beaugerie definition) within 5 years of new diagnosis

We will develop a multivariable prognostic model using prespecified standard predictors (age at recruitment as new diagnosis, smoking, gender, disease status at diagnosis (stricturing disease, perianal disease, severe endoscopic disease, location of disease as L1/L2/L3/L4, initial need for steroid therapy, weight loss of at least 5 kg, CRP, white cell count, faecal calprotectin, haemoglobin and platelets). Continuous variables will be retained where possible, with transformations and polynomial transformations when needed. Categorised variables will be retained as prespecified in clinical report form except where modelling requires combination of categories with small numbers. Missing covariates will be handled via multiple imputation, under the ‘missing at random’ assumption.^44^ We will compare the additive effect on model fit of each MRI score (MEGS, sMaRIA and LI as PCA variables) to the baseline standard model as a linear offset. An increase in model performance will be based on an improvement in the number of patients correctly classified for disabling disease, using models including MRE compared with a standard model. Model performance will be measured using sensitivity, specificity and net benefit. We will also assess difference in model fit using Bayesian Information Criteria (BIC) and we will report c-index for each model. Internal validation using bootstrap samples (sampling with replacement) will use at least 200 or more bootstrap samples until estimates remain stable. Model prediction at 1-year, 2-year and 3-year time horizons will also be reported.

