#### Secondary outcomes

##### Secondary outcome 1

Comparative predictive ability of models incorporating MRI severity scores (MEGS, sMaRIA and LI) when compared with a baseline model of standard characteristics alone, for predicting Montreal B2/B3 disease or Liège severe disease in newly diagnosed patients by 5 years.

Modelling will be conducted as for the primary outcome. Models will only be developed if the number of events/non-events is adequate; if this is not achieved, only descriptive statistics will be provided.

##### Secondary outcome 2

Identification of the best combination of individual MRE features for prediction of disabling CD (all definitions) within 5 years of new diagnosis. PCA will be used to combine multiple MRE parameters into a small number of Eigenscore variables. This allows a larger number of features to be combined without compromising statistical power. The most influential imaging features will be identified for further simplification of MRE variables included in modelling. Methods will be as in the primary outcome, and the statistical significance of including MRE features will be evaluated based on improvement of model fit (BIC) in comparison to the standard model, with additional model performance reported as appropriate.

##### Secondary outcome 3

Average per-patient and national healthcare cumulative costs incurred within 5 years of newly diagnosed CD. Hospital healthcare usage from health economic case report forms (CRFs) will be multiplied by unit costs for relevant items, summed across the 5-year follow-up period, and averaged across the study population (median and mean). Mean costs per patient will be multiplied by the estimated number of CD patients in the UK, stratifying by the presence or absence of disabling disease, to estimate the cost-of-illness following a UK diagnosis (both by UK incidence and prevalence).

##### Secondary outcome 4

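### Improvement from MRE is judged on the number of patients correctly classified, with no requirement that the gain exceed chance; separately, secondary outcome 2 calls a BIC improvement statistical significance

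*Protocol article*

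**What the plan says.** The primary outcome compares prognostic models with and without MRE scores (MEGS, sMaRIA, Lémann Index) for disabling Crohn's disease within 5 years. Under Statistical methods, Primary outcome, the article says that each score is compared with the baseline standard model, and then gives the criterion: "An increase in model performance will be based on an improvement in the number of patients correctly classified for disabling disease". The following sentences add other measures: "Model performance will be measured using sensitivity, specificity and net benefit" and "We will also assess difference in model fit using Bayesian Information Criteria (BIC) and we will report c-index for each model". Internal validation uses at least 200 bootstrap samples.

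Under Secondary outcomes (secondary outcome 2), where individual MRE features are combined by principal component analysis, the wording is different: "the statistical significance of including MRE features will be evaluated based on improvement of model fit (BIC) in comparison to the standard model".

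On size: "The sample size was based on including 207 participants newly diagnosed with CD", and "207 participants will provide 114–124 events and 83–93 non-events".

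**The concern.** The criterion gives a direction (more patients correctly classified) and nothing that separates a real gain from noise. When a variable is added to a model, some patients near the cut-off change class whether or not the variable carries information. The net change is then often positive by chance, and three scores give three opportunities.

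The count also treats a missed case of disabling disease and a false alarm as equally costly. The Discussion gives the study two aims: finding patients who would gain from early advanced therapy, and sparing others unnecessary treatment. Nothing there says that the two errors weigh the same.

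At stake is the answer to the primary question. The last secondary objective also depends on it, because an external evaluation study is to be designed if the predictive potential looks promising.

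The BIC wording is a separate and smaller matter. A reader told that significance was assessed will assume a test at a declared level, usually 5%. BIC is not such a test, and its implied level changes with the number of added terms.

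**Working it through.** **1. The plan's own figure.** 207 × 0.55 = 113.9 and 207 × 0.60 = 124.2 events; the complements are 93.2 and 82.8. The stated 114–124 events and 83–93 non-events are reproduced. No error rate or target gain is attached to the classification criterion.

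**2. How often useless scores meet the criterion.**
- From the article: n = 207, 14 named baseline predictors, three scores, 55–60% prevalence.
- Assumed: logistic model; 17 baseline coefficients (14 predictors, plus 2 extra for location and 1 extra for smoking); SD of the true linear predictor 0.6 or 1.0; risk cut-off 0.40, 0.50 or 0.58; three pure-noise scores correlated 0.5–0.6; scores added by refitting or with the baseline linear predictor as an offset.
- This gives 12 scenarios of 1,500 simulated studies each.

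| Result with useless scores | Range over 12 scenarios |
|---|---|
| One score: count rises | 40–47% |
| One score: count tied | 20–27% |
| One score: count falls | 30–35% |
| At least one of three raises the count | 71–76% |
| All three entered jointly: count rises | 56–62% |

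Simulation error is about √(0.45 × 0.55 / 1500) = 1.3 percentage points. Further runs with 16 baseline coefficients and cut-off 0.5 agree: 42–46% for one score, 72–74% for at least one of three, 55–60% for joint entry.

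**3. After bootstrap optimism correction** (250 studies × 100 bootstraps, cut-off 0.5, SD 0.8): one score 50%, at least one of three 77%, three jointly 44%. The correction removes average overfitting. It does not ask whether a positive difference exceeds its sampling error.

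**4. Relation to net benefit.** With TP and FP the true and false positives and p the risk threshold:

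net benefit = TP/n − (FP/n) × p/(1 − p).

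The change in the number correctly classified is ΔTP + ΔTN = ΔTP − ΔFP. At p = 0.5 the weight p/(1 − p) is 1, so the change in net benefit is exactly the change in count divided by n. At p = 0.40 the weight is 0.40/0.60 = 0.67 and the two differ. It follows that equal weighting is right only at 0.5. It also follows that replacing the count by net benefit without an interval would leave the chance problem in place.

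**5. Scale of a gain beyond chance.** As a rough guide, a McNemar-type comparison needs a net gain of about 1.96 × √(patients who change class). If 10%, 20% or 30% of 207 change class (21, 41 or 62; assumed), that is about 9, 13 or 16 patients. In one set of runs the best of three useless scores gained about two patients on average.

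**6. BIC.** BIC favours the larger model when the likelihood-ratio statistic exceeds df × ln(n), with ln(207) = 5.33.

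| Added terms | Threshold | Implied alpha |
|---|---|---|
| 1 | 5.33 | 0.021 |
| 2 | 10.67 | 0.0048 |
| 3 | 16.00 | 0.0011 |

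In the step 2 simulations BIC favoured a useless score in 1.8–3.2% of studies per score, and at least one of three in 5–8%. With one of three scores truly prognostic (odds ratio 1.65 per SD, assumed), BIC favoured that score entered alone in 58–80% of studies over several runs. With all three entered jointly it favoured MRE in 7–32%, against 56–79% for a 3-df likelihood-ratio test.

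**The case against.** The strongest reply has four parts.

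- **No formal success rule is stated.** A reader might infer that any rise, even of one patient, would be declared an improvement. The article does not say so: the criterion gives a direction, and the primary outcome is comparative predictive ability with no pass/fail threshold. This stands. The percentages describe a literal reading.
- **Companion measures are named.** A reader might infer that the plan ignores the different costs of the two errors. It does not: sensitivity, specificity and net benefit come in the next sentence, and c-index, BIC and bootstrap validation follow. This stands in part, because improvement is still tied to the count and not to those measures.
- **Cut-off, interval and minimum gain may be in the analysis plan, which is not shown.** Their absence from a condensed article is no fault in itself. But the article does not leave the criterion open; it fixes one, and that choice can be judged as written.
- **BIC is not lax.** A reader might infer that BIC would usually miss a real effect, so that the two criteria err in opposite and extreme directions. The primary analysis adds each score to the baseline model. For one term BIC implies alpha 0.021 and found the true score in 58–80% of runs. Its threshold of 5.33 is slightly below the first Holm step for three scores (5.73). The low detection rates belong to joint entry of three terms. That is plausible for secondary outcome 2, where two or three component variables are intended; the reference to PCA variables in the primary analysis is ambiguous. In the primary section BIC is correctly described as a measure of fit, so the mislabel is confined to secondary outcome 2.

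**Conclusion.** The point holds in limited form and should be fixed. The article bases improvement on a raw count of correct classifications, with no requirement that the gain exceed chance. Read literally, one useless score meets this in about 40–47% of studies of 207 patients and at least one of three in about 71–76%. Optimism correction does not lower these figures (50% and 77% in the corrected simulation).

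The figures rest on a logistic model, 16–17 baseline coefficients, cut-offs of 0.40–0.58 and noise scores correlated 0.5–0.6. They varied little over the settings tried.

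The documents do not support saying that the study has a mechanical any-rise success rule, that it cannot answer its question, or that BIC is generally too strict. The BIC fault is one of naming, in secondary outcome 2 only: the implied alpha is 0.021, 0.0048 or 0.0011 for one, two or three added terms. All are below 5%, so false positives are not inflated.

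**What to change.** - **Primary outcome.** Base the claim of improvement on the optimism-corrected difference in net benefit between the MRE and standard models, at a risk threshold fixed before analysis, with a bootstrap 95% confidence interval. Support it with a likelihood-ratio test for each added score, adjusted over the three scores (for example by Holm's method). The investigators should choose and justify the threshold; none is proposed here.
- **Descriptive measures.** Report the number correctly classified, sensitivity, specificity, c-index and BIC as descriptive.
- **Secondary outcome 2.** Either call BIC a fit criterion and drop the reference to statistical significance, or use a likelihood-ratio test for significance and state its level.
- **If the analysis plan already contains a threshold and an interval,** align the published wording with it.

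The cost is wording and slightly more analysis work, with no new data. Improvement becomes harder to claim. The power of the revised criterion at n = 207 has not been calculated here and should be checked before it is adopted.

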### Objectives

#### Primary objective

To improve prediction of disabling CD within 5 years of diagnosis by developing and internally evaluating a multivariable prediction model comprising both existing standard predictors and those based on MRE.

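### The named performance measures include no calibration and no shrinkage, although at least 16 coefficients are estimated on 83–93 non-events, so unshrunken individual risks would be too extreme and no named measure would show it

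*Protocol article*

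**What the plan says.** The primary objective is to improve prediction by "developing and internally evaluating a multivariable prediction model comprising both existing standard predictors and those based on MRE". The methods for the primary outcome repeat this: "We will develop a multivariable prognostic model using prespecified standard predictors". The predictor list begins "age at recruitment as new diagnosis, smoking, gender, disease status at diagnosis (stricturing disease, perianal disease, severe endoscopic disease, location of disease as L1/L2/L3/L4" and continues with initial steroid need, weight loss, CRP, white cell count, faecal calprotectin, haemoglobin and platelets. Transformations and polynomial terms are allowed for continuous variables.

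Each MRE score is then assessed against the baseline model as a linear offset. On performance, the article says "Model performance will be measured using sensitivity, specificity and net benefit"; it also compares fit by BIC, and "we will report c-index for each model". Internal validation uses at least 200 bootstrap samples, but the article does not say which quantities they correct. Calibration, shrinkage, penalisation and recalibration are not mentioned anywhere.

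On size: "The sample size was based on including 207 participants newly diagnosed with CD", and "207 participants will provide 114–124 events and 83–93 non-events". The section on the adequacy of these numbers treats the variables as fixed. It therefore relies on an external-validation rule of 80–100 events, and it applies 10–20 events per variable to the three MRE scores.

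**The concern.** Prespecified variables are not prespecified coefficients. The baseline coefficients are estimated in the same 207 patients, so the external-validation rule does not protect them from overfitting. An overfitted logistic model gives predicted risks that lie too far from the average.

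The c-index depends only on ranking. BIC measures fit penalised for model size. Sensitivity, specificity and net benefit record classification at a threshold. None of these states whether a predicted 20% means 20%.

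This matters because the Discussion intends the prediction to help identify who benefits from early advanced therapy and who can avoid it. The secondary objectives also foresee external evaluation of this same model. Under the offset design, any excess spread in the baseline linear predictor is carried unchanged into the MRE model.

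**Working it through.** **Inputs from the article.** N = 207. Prevalence: "We assume the prevalence of our modified Beaugerie definition of disabling disease will be approximately 55%–60" per cent, with 57% in the cited validation cohort. Baseline predictors: 14 variables. Counting location as 3 parameters and every other variable as 1 gives 13 + 3 = 16 parameters, which is a minimum.

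**The article's own counts reproduce.** Events: 207 × 0.55 = 113.9 and 207 × 0.60 = 124.2. Non-events: 207 × 0.40 = 82.8 and 207 × 0.45 = 93.2. These match 114–124 and 83–93.

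**Non-events per baseline parameter.** 83/16 = 5.2 and 93/16 = 5.8. With one non-linear term for each of the six continuous predictors (22 parameters): 83/22 = 3.8 and 93/22 = 4.2. The 10–20 quoted in the article is met for the three MRE scores alone (83/3 = 27.7), not for the baseline model.

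**Expected calibration slope.** Solve n = P / [(S − 1) ln(1 − R²/S)] for S, with n = 207, P = 16 and R² the Cox–Snell value implied by an assumed true c-index at 57.5% prevalence.

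| Assumed c-index | R² | S (16 parameters) | S (22 parameters) | N for S = 0.90 (16 parameters) |
|---|---|---|---|---|
| 0.65 | 0.068 | 0.49 | 0.41 | 2041 |
| 0.70 | 0.119 | 0.63 | 0.56 | 1124 |
| 0.75 | 0.182 | 0.73 | 0.67 | 711 |
| 0.80 | 0.256 | 0.80 | 0.75 | 478 |
| 0.85 | 0.342 | 0.85 | 0.81 | 335 |

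Check for c = 0.70: 0.119/0.63 = 0.189; ln(1 − 0.189) = −0.209; (−0.37)(−0.209) = 0.0775; 16/0.0775 ≈ 207.

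**Check by simulation.** Unpenalised logistic regression, n = 207, 17 parameters, about half informative, 300 runs, large independent test set. The mean slope in new patients was 0.53, 0.62 and 0.68 at true c-indices of 0.70, 0.75 and 0.80. The formula is therefore, if anything, lenient.

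**Meaning for one patient.** Corrected logit = logit(0.57) + S × [logit(p) − logit(0.57)], with logit(0.57) = 0.282.
- S = 0.63, p = 0.20: 0.282 + 0.63 × (−1.386 − 0.282) = −0.769, a risk of 32%.
- S = 0.63, p = 0.90: 0.282 + 0.63 × (2.197 − 0.282) = 1.488, a risk of 82%.
- S = 0.85: 20% becomes 24%, and 90% becomes 87%.

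**Net benefit (simulation, true c-index 0.75, 17 parameters).**
- Apparent against new patients: 0.305 against 0.233 at threshold 0.5, and 0.173 against 0.070 at 0.7. This gap is optimism.
- Unshrunken against shrunken, both in new patients: 0.391 against 0.396 at threshold 0.3, 0.233 against 0.233 at 0.5, and 0.070 against 0.075 at 0.7.

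**Offset design.** I read the text as carrying the baseline linear predictor forward with coefficient 1. Simulation: n = 207, 57% prevalence, 16 baseline parameters (half informative), one predictive MRE score, true c-index about 0.72, 250 runs.
- Mean slope in new patients: 0.57 for the baseline model and 0.60 with MRE.
- Gain in net benefit from MRE, unshrunken against ideally recalibrated: 0.0030 against 0.0017 (threshold 0.3), 0.0100 against 0.0098 (0.5) and 0.0138 against 0.0118 (0.7).
- In a further simulation of the offset design, shrinking the baseline before adding MRE raised the slope from about 0.56–0.57 to about 0.86, and net benefit at threshold 0.7 from 0.031 to 0.045.

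**The case against.** The strongest reply is that this is silence, not a decision. The article does not call its list of measures complete, and secondary outcome 2 allows further performance measures as appropriate. Calibration plots and shrinkage are also details that an article may leave to an analysis plan, which is not shown. This stands in part: one cannot say that calibration will not be examined, or that the bootstrap will not be used for it. But the article does enumerate the measures for its primary outcome. It also defends the sample size on grounds that overlook the estimated baseline coefficients. Run as written, the plan would not expose the predictable result.

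Two stronger readings are tempting, and the article does not support them.

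- A reader might infer that the reported net benefit must be misleading. The large gap is optimism, which the planned bootstrap can remove if it is applied to net benefit. The loss in true net benefit from not shrinking was 0.005 or less in the 17-parameter simulation at a c-index of 0.75. It was larger (0.014) at threshold 0.7 in one offset simulation.
- A reader might infer that the MRE model, with up to 19 parameters, overfits more and so distorts the comparison. That assumes a joint refit. Under the offset only the MRE terms are newly estimated, and in simulation the slope was no worse with MRE (0.60 against 0.57).

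It is also fair that external evaluation is foreseen before any use, so wrong risks would not pass straight into care.

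**Conclusion.** The point holds as a gap in what the primary analysis names. With 207 patients and at least 16 estimated baseline parameters, the expected slope is about 0.63 at a c-index of 0.70, 0.73 at 0.75 and 0.85 at 0.85. It stays below 0.90 across the whole range of 0.65–0.85. Unshrunken individual risks would be too extreme, and no named measure would show it.

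The consequence concerns the individual risks and the model taken forward to external evaluation. The effect on the MRE comparison is small.

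The size rests on an assumed c-index, a binary logistic model, the minimum parameter count and the offset reading above. Polynomial terms would make it worse. The change is worth making before the analysis is run, but the gap does not invalidate the study.

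**What to change.** Using the bootstrap samples already planned:

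- Report the optimism-corrected calibration slope, calibration-in-the-large and a calibration plot for the baseline model and for each MRE model.
- State that the same optimism correction is applied to sensitivity, specificity, net benefit and the c-index.
- Multiply the baseline linear predictor by the bootstrap slope and re-estimate the intercept before using it as the offset for MRE.

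No further patients or data are needed. The cost is a little more analysis and slightly less favourable reported performance.

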#### Secondary objectives

To improve the prediction of disease phenotype within 5 years, defined by the Montreal behaviour criteria, by developing and internally evaluating a ‘baseline’ multivariable prediction model comprising standard clinicopathological variables.To identify specific combinations of individual MRE findings that best predict disabling CD within 5 years of diagnosis.To estimate the healthcare costs incurred within 5 years of a new diagnosis of CD and to explore patient, imaging and disease characteristics driving higher health economic costs.Assuming promising predictive potential, to then generate a research design for a subsequent prospective study to externally evaluate our MRE-based prediction model if appropriate.

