### Study setting

The study will be conducted at nine UK NHS acute hospitals across England and Scotland, which participated in METRIC, supplemented by two additional NHS acute hospitals who will contribute retrospective accruals.^15 28^ One site from the METRIC trial is not included as they did not recruit any newly diagnosed patients.

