#### Interpretation and blinding

MRE scans will be interpreted by one from a pool of recruitment site radiologists; all are GI radiologists and experienced in MRE, in both clinical and research settings. Radiologists will be allocated MRE scans for scoring. These will be interpreted blinded to all clinical information other than that relevant for the calculation of the relevant index (eg, surgical history for LI).

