#### Primary definition of disabling disease

The primary definition of disabling disease will be a modified version of that described by Beaugerie *et al*.^38^ The original definition has been modified to clarify some of the symptoms and to permit the use of disease-modifying therapy, since this has become a common preventative measure in modern practice. Disabling disease will therefore be defined as any of the following:

Hospitalisation after CD diagnosis for flare or disease complication, as judged by the treating clinician.More than two corticosteroid courses required over 5 years and/or dependence on corticosteroids.Any intestinal resection >50 cm, or surgical operation for perianal disease (examination under anaesthesia without seton placement does not meet this criterion; abscess drainage and/or seton placement does).Chronic disabling symptoms, defined as a cumulative time of over 12 months of one or more of the following:Diarrhoea with nocturnal stool (getting up for a bowel movement after having gone to bed).Urgency (defined as having to rush to the toilet for a bowel movement).Abdominal pain due to intestinal obstruction (requires imaging confirmation or surgical proof).Fever (documented tympanic temperature of >38.0°C or oral temperature of>38.3°C).Fatigue.Joint pain not due to an alternative cause.Uveitis.Pyoderma gangrenosum.

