#### Consensus panel assessment of disease severity

Consensus panels will be convened at each recruitment sites. Panels will comprise, as a minimum, one gastroenterologist and one radiologist, aided by the site research nurse. The consensus panels will review all available clinical information. This will include investigations such as CRP, faecal calprotectin, endoscopy (conventional and capsule), imaging (MRI, US, CT and fluoroscopy), surgical and histopathological findings, clinical activity scores (eg, Harvey-Bradshaw Index) and overall clinical course including outpatient and inpatient clinical records.

Using all the available data, the consensus panels will record the presence or absence of disabling disease, and Montreal classification according to the protocol definitions and the date at which this endpoint was reached.

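### Outcomes are judged hospital by hospital and MRE scores may shift by site or cohort, yet the described models have no site term and no out-of-site check beside the bootstrap

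*Protocol article*

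**What the plan says.** **Outcome.** In the Protocol article, Consensus panel assessment of disease severity, "Consensus panels will be convened at each recruitment sites". Each panel has at least a gastroenterologist and a radiologist and applies the protocol definitions. Under Primary definition of disabling disease, one criterion that suffices alone is "Hospitalisation after CD diagnosis for flare or disease complication, as judged by the treating clinician".

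**MRE scores.** Under Interpretation and blinding, "MRE scans will be interpreted by one from a pool of recruitment site radiologists". Scans are allocated to these radiologists, but the rule is not given; readers are blinded to clinical information that the index does not need. Table 2 gives MEGS points for both the amount and the pattern of contrast enhancement. The Sequences text exempts retrospective scans from diffusion-weighted imaging only, whereas the footnote to Table 1 also makes the pre- and post-gadolinium sequence optional for them.

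**Sites.** Study setting names nine METRIC hospitals, "supplemented by two additional NHS acute hospitals who will contribute retrospective accruals".

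**Analysis.** Statistical methods, Primary outcome, lists the standard predictors one by one, then multiple imputation, the MRE terms, sensitivity, specificity, net benefit, BIC and c-index. Validation is described as "Internal validation using bootstrap samples (sampling with replacement", with at least 200 samples. Neither site nor reader appears.

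**Use of the result.** If predictive potential is promising, the last of the Secondary objectives is "to then generate a research design for a subsequent prospective study to externally evaluate our MRE-based prediction model if appropriate".

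**The concern.** Outcome rates can differ between hospitals because panels, admission thresholds and record-keeping differ. Score levels can differ because of readers, scanners (1.5 T or 3 T) or the availability of contrast. If both shift by hospital, a score with no prognostic value within a hospital can still correlate with outcome across hospitals. A model without a site term credits that correlation to MRE.

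The planned validation would not show this. A bootstrap that resamples patients corrects for overfitting, but every resample draws on the same hospitals, so the between-hospital association is present in both fitting and testing. The apparent gain would then inform the judgement on whether an external study is worthwhile.

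**Working it through.** **Inputs from the article.** "The sample size was based on including 207 participants newly diagnosed with CD" (Sample size and justification); prevalence 55–60% (Assumptions); 9 + 2 = 11 hospitals (Study setting).

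**Reproducing the plan's figures.** Events: 207 × 0.55 = 113.9 and 207 × 0.60 = 124.2, so 114–124. Non-events: 207 × 0.40 = 82.8 and 207 × 0.45 = 93.2, so 83–93. Both agree with the article. Per hospital this averages 207/11 = 18.8 patients and 83/11 = 7.5 to 93/11 = 8.5 non-events.

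**How contrast could move MEGS.** Table 2 gives up to 3 points for amount and 2 for pattern, 5 in all. The mural maximum is 3+3+3+3+2 = 14 in a small-bowel segment and 14+3 = 17 in a colonic one. Contrast items are thus 5/14 = 36% or 5/17 = 29% of the segmental maximum. The article does not say how a scan without contrast is scored. The target is 76 retrospective patients (76/207 = 37%), and cohort coincides with hospital at the two added sites.

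**Size of the false gain (assumed inputs).** The documents give no intraclass correlation (ICC), so a range was simulated: 207 patients, one clinical predictor, one MRE score with no within-site value, logistic models, 4,000 studies per setting. An outcome ICC ρ means a site log-odds variance of ρ(π²/3)/(1−ρ): ρ = 0.05 gives SD 0.42, and ρ = 0.10 gives SD 0.60. A score ICC of 0.10 or 0.20 is a shift of √(0.10/0.90) = 0.33 or √(0.20/0.80) = 0.5 within-site SD. BIC prefers the MRE model when the likelihood-ratio statistic exceeds ln 207 = 5.33, which has a chance of about 2% for one useless term.

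| Setting (outcome ICC / score ICC) | Test p<0.05 | BIC prefers MRE |
|---|---|---|
| No site effects | 5.4% | 2.3% |
| 0.05 / 0.10, score shift follows site, 11 equal sites | 6.0% | 2.9% |
| 0.10 / 0.20, same | 8.2% | 4.0% |
| 0.10 / 0.20, 11 unequal sites | 9.0% | 4.5% |
| 0.10 / 0.20, 9 unequal sites | 10.1% | 4.9% |
| 0.20 / 0.30, 11 unequal sites | 16.7% | 9.8% |
| 0.10 / 0.20, unequal, scans spread over readers | 4.9% | 2.1% |

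The BIC column matters most, because the article names BIC and no 5% test. A separate set of runs at site log-odds SD 0.4–0.6 and score shift 0.33–0.5 SD, the same moderate range, gave a false BIC gain of 2–3%, no different from no site effects. It reached about 11% only at 0.8 and 1.0. A shift of 1.0 within-site SD is an ICC of 1/(1+1) = 0.50, which is extreme. The moderate range is best read as 2–5%.

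**Can the bootstrap see it?** In 200 studies, site effects on score and outcome were forced to align (site log-odds SD 0.6). BIC preferred the useless score in 22.5%. The mean patient-level bootstrap-corrected c-index gain stayed positive (+0.005), while the within-hospital gain under leave-one-site-out was −0.012.

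**With a real effect** (log odds ratio 0.35 per SD), the bootstrap-corrected gain was 0.012 against 0.009 in new sites at site log-odds SD 0.5 and shift 0.5, and 0.008 against 0.0015 at 0.8 and 1.0.

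**Does a site term help?** A site random intercept brought the false BIC gain back to about 3% even in the extreme setting.

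**The case against.** Three points have force.

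First, a reader might infer that radiologists score their own hospital's scans. The article says only that the pool is drawn from site radiologists and that scans are allocated. If scans are spread over readers, the reader-driven inflation disappears (4.9% and 2.1% in the table). Scanner, cohort and contrast differences could still leave a site shift, but the article does not establish one.

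Second, a reader might infer that the plan treats the 207 patients as independent. That rests on silence: no resampling unit is named, the SAP is not shown, and it may specify site terms or resampling by hospital. What can be said is that the described analysis contains neither, and that sampling with replacement, unqualified, ordinarily means sampling patients.

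Third, the plan has safeguards: blinded and experienced readers, tabulated scoring, a minimum sequence set and written outcome criteria. The primary objective also claims internal evaluation only and leaves other hospitals to a later study. The safeguards make large shifts less likely. Deferring external evaluation is reasonable, but it does not answer whether the internal gain is MRE value or hospital differences.

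**Conclusion.** The point holds as a limited one. Outcome judgement is local by design, MRE scores may shift by site or cohort, and the analysis as described could not reveal a between-site association. The risk is negligible to modest for moderate site shifts (false BIC gain about 2–5% against about 2%). It is material only for large shifts (about 10–11%) or aligned ones (22.5% in the forced case). All of these rest on assumed site effects.

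The documents do not support saying that a false gain is likely, or that the bootstrap is wrong for its purpose of correcting overfitting. Nor do they show that the decision on an external study rests solely on the bootstrap-corrected gain. The case for change is that the check is cheap, not that the planned result is unsound.

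**What to change.** 1. **Statistical methods, Primary outcome:** add a site random intercept to both the standard and the MRE models, as a sensitivity analysis of added value. It absorbs a cohort difference only where a hospital supplies one cohort.
2. **Same section:** beside the bootstrap, report leave-one-site-out c-index, calibration and net benefit, pooled over hospitals. Form the c-index from pairs within a hospital, since pairs across hospitals would let the between-site signal back in. Read these results together with the bootstrap when judging whether potential is promising. They should not be the sole basis: with about 8 non-events per hospital they are too noisy.
3. **Interpretation and blinding:** state the allocation rule, and allocate scans across the existing reader pool at random or balanced over sites.
4. **Sequences and Table 1:** reconcile the text with the footnote on gadolinium imaging for the retrospective cohort. Reconcile the site descriptions too: Study design has METRIC in eight centres, Study setting has nine METRIC hospitals with one excluded, and Sample size draws the retrospective cohort from METRIC sites although two others are added.

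Cost: analysis-plan wording, some computing and an allocation list, with no new patients or data. The downsides are noisy out-of-site estimates from about 11 small sites and a little lost precision from the site term.
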